### Follow-up and data collection

Patients will be followed-up until 60 days or death, whichever comes first. In this trial, data collection will occur on days 1, 3, 5, 8, 15, 22, 30, and 60. The schedule of data collection is shown in Table 2. Efficacy assessment includes all-cause mortality, clinical status (8-point ordinal Scale), APACHE-II scores, oxygenation index, changes in chest CT scan, and the clinical performance of nasopharyngeal severe acute respiratory syndrome coronavirus 2 reverse transcription polymerase chain reaction (NP SARS-CoV-2 RT-PCR) testing.

**Table 2 Tab2:** Schedule of patient assessments

Time Point	Screening	Treatment Period		Safety Follow-up				
		Baseline (Day 1)	Day 2-Day 7 (up to Day 14)	Day 15 ± 2	Day 22 ± 2		Day 30 ± 3	Day 60 ± 3
Informed consent	●							
Verify eligibility criteria	●							
Demographics	●	●						
Medical History	●	●						
Targeted physical exam	●	●						
Review SARS-CoV-2 results	●	●						
Review X-ray or CT if applicable	●	●						
Vaccination status	●	●						
Vital signs including SpO_2_	●	●	Once a day till discharge	●			●^a^	
Targeted Physical Examination		●	●	●				
Clinical data collection		●	●	●	●^a^			
AEs evaluation		●	Once a day till discharge	●	●		●	●
Concomitant medication review		●	Once a day till discharge	●	●		●	
X-ray or CT			●^a^	●^a^				
12-ECG	The decision is made by professional investigators							
Hematology, urine routine, and coagulation action test	●	●	Day 3, 5, 8 (all ± 1 day)	●		●		
Pregnancy test for females of childbearing potential	●					●		
Nasopharyngeal swab		●	Day 3, 5, 8 (all ± 1 day)	●		●^a^		

*AEs* adverse events, *CT* computed tomography, *ECG* electrocardiography, *PI* principal investigator, *SARS-CoV-2* severe acute respiratory syndrome coronavirus 2

^a^ optional; ● mandatory

The safety assessment includes general vital signs, physical examination, 12-lead electrocardiography (ECG), laboratory examination (routine blood test, blood biochemical, routine urine test, and biomarker analysis) chest radiography, CT scans, and AEs. The physical examination includes assessments of the eyes, ears, nose, mouth, throat, cardiovascular, respiratory, gastrointestinal, genitourinary, hematologic/lymphatic, endocrine, and neurological.

The 8-point ordinal scale is an assessment of the clinical status at the first assessment of a given study day. The scale is defined as follows: (1) Death; (2) Hospitalized, on invasive mechanical ventilation or ECMO; (3) Hospitalized, on non-invasive ventilation or high flow oxygen devices; (4) Hospitalized, requiring supplemental oxygen; (5) Hospitalized, not requiring supplemental oxygen- requiring ongoing medical care (COVID-19 related or otherwise); (6) Hospitalized, not requiring supplemental oxygen, and no longer requires ongoing medical care; (7) Not hospitalized, limitation on activities; (8) Not hospitalized, no limitations on activities [21].

APACHE II score is a severity score and mortality estimation tool developed from a large sample of ICU patients, which consists of an acute physiology score (APS), the age of the patient, and chronic health points. And APACHE II score is made of 12 physiological variables and 2 disease-related variables. The maximum APACHE-II score is 71, though it is rare for a patient to score higher than 55. When APACHE II scores are combined with an accurate description of the disease, they can prognostically stratify acutely ill patients and assist investigators in comparing the success of new or differing forms of therapy [22, 23].

Nasopharyngeal swabs will be performed following a standardized procedure in this trial [24]. In addition, the result of NP SARS-CoV-2 RT-PCR will be adopted, if patients have already tested for NP SARS-CoV-2 RT-PCR no more than 48 h before the first drug administration. The viral clearance of COVID-19 in the treatment period defines as the results of both tests (the first test and retested 24 h later) being negative SARS-CoV-2 RT-PCR test or Ct values > 35.

### Plans to promote participant retention

If patients are discharged from the hospital and are unable to return for follow-up as scheduled due to being isolated in the COVID-19 epidemic, a visit on days 15 or 30 should be performed as quickly as possible after ending the isolation period. A face-to-face visit is preferred on day 22, nevertheless, quarantine and other factors should also be considered for return visit patients and a remote visit may be optional. The telephone visit may be conducted on day 60.

### Data management

All the data obtained for analysis in the clinical study described in this protocol will be recorded in the paper case report format (CRF). All paper CRFs are sent to Contract Research Organization (CRO) and then entered into the electronic data capture (EDC) system. Any fill-in, change, or correction to a CRF will be decided by the investigator or a person designated by the investigator. Investigators have demonstrated the accuracy of all recorded data. The Data in this study will be entered directly into CRFs and not be used as original medical records unless otherwise stated. The inspector will check the CRF to make sure all data recorded in the CRF is consistent with the original material. The data will be validated by the data management plan. To ensure the accuracy of the data, the quality control process will run through every stage of data processing.

### Sample size calculation

The primary endpoint of this study is the 30-day all-cause mortality. Based on a previous study, the all-cause mortality rate of hospitalized patients infected with COVID-19 is approximately 7.3% to 14.1% [25, 26]. Assuming that the proportion of all-cause mortality is 12% in severe or critically ill patients infected with COVID-19 under standard therapy, it is expected that the proportion of all-cause mortality can be reduced to 2% after treatment with proxalutamide. The probability of a type I error is set at 0.05 (*p* = 0. 05) with a power of 80%, and 58 patients will be required to be enrolled based on the exact probability method. It is expected that the drop-out rate of enrolled subjects will be ≤ 10%. Thus, this study is planned to recruit 64 severe or critically ill patients with COVID-19.

### Statistical analysis

All efficacy analysis results are analyzed in the full analysis set (FAS) and per-protocol set (PPS). The FAS is defined as all randomized patients who received at least one dose of the study drug. The PPS is defined as all patients who completed the treatment without serious violation of the protocol. The safety analysis will be performed based on the FAS and no imputation will be made for missing safety data. Categorical data will be expressed as numbers and percentages, and quantitative data will be expressed as means ± standard deviation (SD), median, interquartile range (IQR) values, or minimum and maximum. The primary outcome will be an analysis of the percentage of 30-day all-cause mortality. The analysis of efficacy in the secondary endpoint measures will be based on their variable attributes in an appropriate way. For binary variables, the exact probability method will be used to calculate the probability of the subject with clinical deterioration. For continuous variables, the value of actual measured values and the chances from the baseline will be summarized. For rank variables such as changes in the score of the 8-point order scale, the paired Signed Rank Test method will be used. For time-to-event variables, the Kaplan–Meier method will be used to estimate the median and Kaplan–Meier graphs will be provided. All statistical analyses will be performed using Statistical Analysis System 9.4 (SAS Institute, Inc, Gary, NC), and statistical significance was set at *p* < 0.05.

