## Methods

### Study design

This is a single-arm, open-label, single-center prospective exploratory trial to assess the efficacy and safety of proxalutamide in severe or critically ill COVID-19 subjects. Recruitment started on 16 May 2022 and is foreseen to end on 16 May 2023. This trial is designed according to the Standard Protocol Items: Recommendations for Interventional Trials (SPIRIT) 2013 Statement [18]. In addition, this trial is registered in the China Clinical Trial Registry (ChiCTR2200061250).

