### Intervention

Eligible patients will receive Proxalutamide (300 mg, Kintor Pharmaceuticals Ltd., Suzhou, China) plus standard of care. Proxalutamide will be administered orally once daily at the same time each day (± 2 h according to medication scheduling). The duration of the study treatment will last for 7 days and can be extended to 14 days at the discretion of the investigator.

Any dose that is missed and delayed may be administered as soon as possible on the same calendar day. When it is almost time for the next scheduled dose (within 4 h), we recommend skipping the missed dose and taking the next dose instead. The missed dose will not be made up if it is not given on the same calendar day.

Use of antipyretic medications (eg, paracetamol) or other adjunctive medications (eg, vitamins) is allowed before enrollment. Use of the following drugs is allowed during the trial period: treatment drugs against adverse events as well as underlying conditions (used stably for at least 3 months); oral contraceptive; convalescent plasma from recovered COVID-19 patients; anti–SARS-CoV-2 monoclonal antibodies; corticosteroids. Moreover, participants are advised to avoid the consumption of grapefruit, carambola, bigarade, or their juice, which belongs to CYP3A4 inhibitors and can increase exposure to proxalutamide. Allowable drugs for severe or critically ill patients with COVID-19 are administered based on investigators’ clinical judgment and clinical practice guidelines [20].

Discontinuance criteria of treatment are as follows: (1) If participants are tested negative for SARS-CoV-2 by RT-PCR assay or Ct values > 35, and repeated testing is still negative or Ct values > 35 after 24 h, the treatment will be discontinued by the investigator; (2) If grade 3–4 drug-related adverse events (AEs) occur during treatment, proxalutamide will be permanently discontinued.

It is important for the patient to fully understand the importance of conducting the trial, medicine administration on time, and follow-up on schedule during the trial for enhancing patient adherence. The subjects will be required to take the medicine according to the regulations, fill in the patient diary card on time, and attend the follow-up as required.

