### Confidentiality

All communications, reports, and subject samples will be identified by site number, code number, and initials to maintain subject confidentiality. All records will be kept confidential to the extent permitted by law. If a waiver or authorization separate from the statement in the informed consent is required for permitting access to the medical records of a subject, the investigator will obtain such authorization before enrolling the subject in the study. The investigator should keep a separate log of subjects, codes, names, and addresses. Documents that identify the subject by name (eg, the informed consent forms) will be kept in strict confidence.

The sponsor and its business associates agree to keep all subject information confidential. Data resulting from analyses will be entered into a database that is not accessible to the public. Subject data will be identified only by the subject screen number, randomization number, and initials, and not by any other annotation or identifying information. The sponsor and its business associates will take every possible step to reduce the risk of releasing information to the public that would enable subjects to be personally identified.

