Despite the above strengths, there are still some limitations in the present study. Firstly, our sample size was small and the trial was conducted at one center. However, as the COVID-19 pandemic is a sudden and temporary event, the center for accepting and treating severe or critically ill patients with COVID-19 is limited and temporally, meanwhile, the number of recruited severe or critically ill patients at clinical centers may be low. Secondly, this trial did not include a control group, therefore, reducing the generalizability of our results. Because there is no approved effective conventional treatment for patients with severe or critical COVID-19. Given the ethical considerations of protecting the maximum benefits of participants and the objectives (rapid discovery of proxalutamide efficacy) of this investigator-initiated clinical trial, no control group was recruited for this study. Randomized controlled trials will continue to be conducted in the future to assess the effect of proxalutamide. Thirdly, this is an open-label trial, considering severe or critically ill patients with COVID-19 may deal with invasive treatment delivered in the ICU (including ECMO), which is undoubtedly more difficult or impossible to conduct a blinded trial. But blind will be maintained for all other members of the clinical and research team, such as statistical staff, to minimize bias.

In summary, the present trial is the first to investigate the efficacy and safety of proxalutamide in severe or critically ill patients with COVID-19. The findings of this study might provide convincing evidence regarding the efficacy and safety of proxalutamide on severe or critically ill patients with COVID-19.

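### The per-protocol set requires completed treatment with no exception for death, so patients who die on treatment drop out of a mortality analysis

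*Protocol article*

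**What the plan says.** The Statistical analysis section of the protocol article sets two populations for efficacy: "All efficacy analysis results are analyzed in the full analysis set (FAS) and per-protocol set (PPS". The per-protocol rule is "The PPS is defined as all patients who completed the treatment without serious violation of the protocol". It makes no exception for patients who die during the course.

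The full analysis set is worded as "The FAS is defined as all randomized patients who received at least one dose of the study drug", and the same set serves safety: "The safety analysis will be performed based on the FAS".

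Under Intervention, the course is 7 days and may be extended to 14. The same section gives two routes to an early stop. One is viral clearance, confirmed by a repeat test after 24 hours. The other is toxicity: "If grade 3–4 drug-related adverse events (AEs) occur during treatment, proxalutamide will be permanently discontinued".

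The primary endpoint is death from any cause by day 30 (Study endpoints). The sample size section assumes 12% mortality under standard therapy and 2% on the drug.

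**The concern.** Completion of treatment is a post-baseline condition, and a patient who dies on treatment necessarily fails it. Followed as written, the rule removes such patients from both the numerator and the denominator of the per-protocol mortality figure, although each is a primary-endpoint event.

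In a two-arm trial, a control group under the same rule might absorb part of the distortion. Here the Discussion confirms that "this trial did not include a control group", so the per-protocol percentage can only be set against the assumed 12%. If deaths are lost more often than survivors, an inert drug will look as if it lowers mortality. The patients are severe or critically ill, so deaths during the course are plausible.

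A smaller point concerns wording. The full analysis set is defined through randomisation, whereas Study design says "This is a single-arm, open-label, single-center prospective exploratory trial".

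**Working it through.** **1. The plan's own figure.** Inputs from the sample size section: 12% versus 2%, type I error 0.05, power 80%, exact method, 58 patients, drop-out up to 10%, 64 recruited. The section does not state sidedness. Take an exact binomial test that declares benefit when deaths ≤ c, with 0.025 in the lower tail:

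- N=57: P(deaths ≤ 2 | 12%) = 0.0263, above 0.025, so c=1 and power at 2% is 0.684.
- N=58: P(deaths ≤ 2 | 12%) = 0.0239, so c=2 and power at 2% is 0.890.

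The smallest N with at least 80% power is 58, so the stated figure reproduces under a two-sided 0.05 test. Then 58 × 1.10 = 63.8, rounded to 64. The same test is used below. It is inferred from the sample size section, because the analysis section says only that the percentage will be analysed.

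**2. The threshold at N=64.** P(deaths ≤ 2 | 12%) = 0.0132 and P(deaths ≤ 3 | 12%) = 0.0428. Benefit therefore needs at most 2 deaths, against 64 × 0.12 = 7.7 expected if the drug does nothing. With every dosed patient kept, the false-positive chance is 1.3%.

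**3. Effect of the completion rule.** Assume an inert drug and true mortality of 12%. Let f be the share of 30-day deaths excluded because they occur before completion. Let g be the share of survivors excluded because of an early protocol-specified stop. The documents give neither, so both are assumptions.

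PPS mortality = 0.12(1−f) / [0.12(1−f) + 0.88(1−g)]

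- f=25%, g=0: 0.09 / (0.09 + 0.88) = 9.3%
- f=50%, g=0: 0.06 / (0.06 + 0.88) = 6.4%
- f=50%, g=25%: 0.06 / (0.06 + 0.66) = 8.3%
- f=25%, g=25%: 0.09 / (0.09 + 0.66) = 12.0%

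When g=f the factor (1−f) cancels and the result is 12% whatever its value. If g exceeds f, PPS mortality is above 12%.

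**4. False-positive chance.** The number excluded is binomial with N=64 and probability 0.12f + 0.88g. For each resulting set size, the exact cut-off against 12% (lower tail 0.025) is found, and the probability of meeting it is averaged over set sizes.

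| f | g | PPS mortality | False-positive chance |
|---|---|---|---|
| 0 | 0 | 12.0% | 1.3% |
| 10% | 0 | 10.9% | 2.6% |
| 25% | 0 | 9.3% | 6.4% |
| 25% | 25% | 12.0% | 1.4% |
| 50% | 0 | 6.4% | 23.8% |
| 50% | 25% | 8.3% | 6.5% |

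With N=58 and g=0, the chance is 2.4% at f=0, 3.9% at f=25% and 13.5% at f=50%.

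**5. Plausible values of f.** If deaths were spread evenly over 30 days, f would be 7/30 = 23% for the default course and 14/30 = 47% for the extended one. These are illustrations only, since the documents do not describe the timing of deaths.

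**The case against.** The strongest reply is that the analysis which keeps all deaths is already planned. The FAS retains every dosed patient, so the problem is confined to the second set, and a reader would see the two figures diverge. This stands and limits the severity.

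A reader might infer that PPS mortality is biased downwards by construction. The documents do not support that. If completion is read strictly, survivors stopped early for viral clearance also leave the set, which pushes mortality back up. If protocol-specified stops count as completion, that offset disappears, but so does the claim that patients stopped for toxicity are excluded. The protocol does not say which reading applies. What survives is that a death on treatment is not completion on either reading, and that any cancellation would be accidental.

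A reader might also quote a false-positive chance of about 60%. That needs f=75% and g=0 (PPS mortality 3.3%), so three quarters of 30-day deaths would precede the end of a course that is 7 days by default. Nothing in the documents suggests this.

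Nor does the text show that the two sets have equal standing, or that the more favourable result will be emphasised. It does not rank them, and naming the primary set is commonly left to an analysis plan, which is not shown here. The point rests on the per-protocol rule that is stated.

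Finally, reading the FAS as empty because nobody is randomised goes too far. The intended set, everyone with at least one dose, is clear. The Confidentiality section has the same slip: "Subject data will be identified only by the subject screen number, randomization number, and initials".

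**Conclusion.** The concern holds for the per-protocol definition. As written, it makes membership depend on the primary outcome, and there is no control arm to balance the effect. For an inert drug at 12% mortality and N=64, the results range from no bias (g=f) to an apparent mortality of 6.4% with a 23.8% false-positive chance (f=50%, g=0), with intermediate cases near 6.5%. These figures depend on assumed f and g and on a test inferred from the sample size section. The FAS result is unaffected at 1.3%, and the sample size of 58, or 64 with drop-out, does not change.

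This should be fixed, but it does not invalidate the trial's mortality analysis. The reference to randomisation in the FAS is a wording correction only.

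**What to change.** Base the 30-day mortality conclusion on the FAS and label the PPS supportive. Define the PPS as FAS patients with no serious protocol violation up to the earliest of death, a protocol-specified stop or the planned end of treatment, so that none of these events excludes a patient. In the FAS definition, refer to enrolled rather than randomised patients who received at least one dose.

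The cost is about two sentences and no new data. The per-protocol mortality figure may become less favourable. The Trial status section reports that all 64 patients have been recruited, so the change should be recorded before the outcome data are analysed.

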### Study endpoints

The primary endpoint of this study is 30-day all-cause mortality. Secondary outcomes include the following:(1) 60-day all-cause mortality;(2) The proportion of clinical deterioration, which is defined as the need within 30 days after administration for admission to the intensive care unit or invasive mechanical ventilation/ extracorporeal membrane oxygenation (ECMO), or all-cause mortality;(3) Mean change in clinical status using the 8-point-ordinal-scale from day 1 (baseline) to day 15 and day 22 (optional);(4) Time to sustain clinical recovery (determined using an 8-point ordinal scale);(5) Percentage of subjects reaching sustained clinical recovery (determined using an 8-point ordinal scale) on days 5, 8, 15, and 22 (optional);(6) Mean change in the Acute Physiology and Chronic Health Evaluation II (APACHE-II) scores from day 1 (baseline) to days 15 and 22 (optional);(7) Changes in oxygenation index measured by blood gas analysis or blood oxygen saturation from day 1 (baseline) to days 3, 5, 8, 15, and 30 (optional);(8) Changes in chest CT scan (optional) from baseline to day 8 or 15;(9) Percentage of subjects confirmed negative for SARS-CoV-2 RT-PCR by nasopharyngeal (NP) swab on days 3, 5, 8, 15, and 30 (optional);(10) Change in Ct values of SARS-CoV-2 RT-PCR on days 3, 5, 8, 15, and 30 (optional);(11) Safety assessments (eg, AEs, serious AEs, and abnormal laboratory data) from the time of SARS-CoV-2 RT-PCR turned negative to day 30.

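### Patients who die before completing treatment are dropped from the per-protocol set, so per-protocol 30-day mortality, a second reading of the primary endpoint, can understate true mortality

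*Protocol article*

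**What the plan says.** All from the protocol article.

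- Statistical analysis, sets used: "All efficacy analysis results are analyzed in the full analysis set (FAS) and per-protocol set (PPS").
- Statistical analysis, PPS: "The PPS is defined as all patients who completed the treatment without serious violation of the protocol".
- Statistical analysis, FAS: "The FAS is defined as all randomized patients who received at least one dose of the study drug". Nobody is randomized in this single-arm trial. That is a separate wording slip, and I read the FAS as all dosed patients.
- Study endpoints: "The primary endpoint of this study is 30-day all-cause mortality".
- Intervention, duration: "The duration of the study treatment will last for 7 days and can be extended to 14 days at the discretion of the investigator".
- Intervention, early stops: after viral clearance, "repeated testing is still negative or Ct values > 35 after 24 h, the treatment will be discontinued by the investigator"; after a grade 3–4 drug-related adverse event, "proxalutamide will be permanently discontinued". The article does not say whether either stop counts as completing treatment.
- Sample size calculation, the yardstick: "Assuming that the proportion of all-cause mortality is 12% in severe or critically ill patients infected with COVID-19 under standard therapy", with an expected 2% on proxalutamide.

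**The concern.** The endpoint clock starts at the beginning of treatment and runs for 30 days. Entry to the PPS is settled later, when the course is finished. Someone who dies while still being dosed has not finished, and so disappears from both the numerator and the denominator of the per-protocol rate. The set is selected partly on the outcome it is meant to measure.

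In a randomized trial a comparator would lose its early deaths under the same rule. Here the only comparison is with a fixed 12%, so nothing offsets the loss. The patients are severely or critically ill, so deaths during a 7- to 14-day course are plausible. At stake is a per-protocol mortality figure that sits beside the FAS figure and may look better only because early deaths were removed.

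**Working it through.** **1. The plan's own sample size.** Inputs from the Sample size calculation section: 12% against 2%, type I error 0.05, power 80%, exact method. The number of sides is not stated. With 0.025 in the lower tail, the smallest n with at least 80% power is 58: reject at 2 or fewer deaths, P(X ≤ 2 | 58, 0.12) = 0.0239, power P(X ≤ 2 | 58, 0.02) = 0.890. With 0.05 in the lower tail, 38 would already suffice. So 58 reproduces with the 0.025 tail, which I use below. The planned 64 follows from 58 × 1.1 = 63.8.

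**2. Share of deaths before completion, f.** The article does not give it. As an assumption, take a constant daily hazard that yields 12% at 30 days.
- To day 7: (1 − 0.88^(7/30)) / 0.12 = 0.0294 / 0.12 = 0.245.
- To day 14, if every patient were extended: (1 − 0.88^(14/30)) / 0.12 = 0.0579 / 0.12 = 0.483.

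**3. Expected PPS mortality.** Let p = 0.12 and let s be the share of 30-day survivors excluded from the PPS for any reason. Then

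PPS mortality = p(1 − f) / [p(1 − f) + (1 − p)(1 − s)].

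With s = 0 this is p(1 − f) / (1 − pf):
- f = 0.245: 0.0906 / 0.9706 = 9.3%.
- f = 0.483: 0.0621 / 0.9421 = 6.6%.

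With s = 0.10 the survivor term is 0.88 × 0.90 = 0.792:
- f = 0.245: 0.0906 / 0.8826 = 10.3%.
- f = 0.483: 0.0621 / 0.8541 = 7.3%.

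When s = f the factors cancel and the result is 12%. When s > f it exceeds 12%. For example, f = 0.245 and s = 0.30 give 0.0906 / (0.0906 + 0.616) = 12.8%.

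**4. Chance of a falsely significant PPS result.** With 64 dosed, the number excluded, e, is binomial with probability pf + (1 − p)s. Deaths among the remaining 64 − e are binomial at the PPS rate from step 3. For each e, the test rejects at the largest death count whose lower-tail probability under 12% is at most 0.025 (2 deaths for 58 to 64 patients, 1 death for 45 to 57). Summing over e:

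| f | s | PPS mortality | Falsely below 12% |
|---|---|---|---|
| 0 (as in the FAS) | 0 | 12.0% | 1.3% |
| 0.245 | 0 | 9.3% | 6.3% |
| 0.245 | 0.10 | 10.3% | 3.1% |
| 0.483 | 0 | 6.6% | 22% |
| 0.483 | 0.10 | 7.3% | 11% |

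**5. In counts.** Eight deaths among 64 dosed is 12.5% in the FAS. If 4 of the 8 die before completing, the PPS shows 4/60 = 6.7%. To return to 12.5%, 28 of the 56 survivors would also have to be excluded (4/32). That is half of them, which matches s = f = 0.5.

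**The case against.** The case on the other side is substantial, and much of it stands.

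- **The FAS keeps every death.** It is reported for every efficacy result, so no death is hidden. Safety is analysed on the FAS and discontinuations for adverse events are tabulated, so toxicity is not lost either. This stands: the defect is confined to PPS mortality.
- **Ranking the sets is commonly left to the analysis plan, which is not shown.** This also stands, and I do not count the missing ranking as the fault. The fault is the stated PPS rule and its stated use for all efficacy results. An analysis plan that followed this text would inherit it.
- **The article gives no decision rule for the PPS.** The 12% appears only under Sample size calculation, and the trial is called exploratory. So the error rates above show what the design's own test would do if applied to the PPS. They are not rates the plan commits to.
- **A reader might infer that every death on days 1 to 14 is removed.** The text does not support that. Completion is undefined for the discretionary extension, so a patient who dies on day 10 after a full 7-day course may count as a completer. So may one who dies after a stop for viral clearance.
- **A reader might infer that PPS mortality is too low by construction.** That also fails. Surviving non-completers are excluded as well, which pushes the rate up. With f = 0.245, excluding 10% of survivors brings the error rate to about 3%, and excluding 30% reverses the bias.

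What remains is that a patient who dies within the base 7-day course cannot be said to have completed it, and no text keeps such a patient in the PPS.

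**Conclusion.** The point holds in a limited form. The PPS is partly selected on the primary endpoint, so its 30-day mortality can understate the true rate. The same applies to 60-day mortality. The FAS estimate is sound.

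Under an inert drug with 64 dosed, the understatement runs from 12% to 9.3% (7-day case) or 6.6% (everyone extended to day 14) if no survivor is excluded, and to 10.3% or 7.3% if 10% of survivors are. The chance of a falsely significant PPS result is about 6% or 22%, falling to about 3% or 11%, against 1.3% in the FAS. These figures rest on four assumptions: constant hazard, true mortality of 12%, the 0.025 lower tail, and the assumed share of survivors excluded.

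More dramatic illustrations are possible. If 70% of deaths came before completion, PPS mortality would be 3.9% and the error rate 51%. Nothing in the article supports so high a share, and the conclusion does not need it.

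**What to change.** In the analysis-set definitions under Statistical analysis:

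1. Name the FAS as the set on which the conclusion about 30-day and 60-day mortality rests, and label PPS mortality as supportive.
2. State that death during the dosing period is not a reason for exclusion from the PPS: a patient who followed the protocol up to death stays in.

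This takes about two sentences and needs no new data, visits or change in treatment. The article reports 64 participants recruited by 16 May 2023, so the change should be made and dated before the mortality analysis is run. The cost is a less favourable PPS mortality figure.

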### Trial status

Participant recruitment started on 16 May 2022, with 64 participants recruited by 16 May 2023.

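### The completers-only per-protocol set lets death during treatment decide who is counted in the 30-day mortality analysis

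*Protocol article*

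**What the plan says.** On analysis sets, the Statistical analysis section says: "All efficacy analysis results are analyzed in the full analysis set (FAS) and per-protocol set (PPS"). The FAS requires at least one dose. For the other set: "The PPS is defined as all patients who completed the treatment without serious violation of the protocol". The section neither ranks the two sets nor says how a death during the course is classified.

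On treatment, the Intervention section says: "The duration of the study treatment will last for 7 days and can be extended to 14 days at the discretion of the investigator". It also lists two early stops. One is for viral clearance (negative or Ct above 35, confirmed after 24 hours). The other is permanent discontinuation for a grade 3–4 drug-related adverse event. It does not say whether a patient stopped under either rule has completed treatment.

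On endpoints, the Study endpoints section says: "The primary endpoint of this study is 30-day all-cause mortality". Secondary endpoints include 60-day all-cause mortality and clinical deterioration, a composite whose components include "invasive mechanical ventilation/ extracorporeal membrane oxygenation (ECMO), or all-cause mortality".

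The only benchmark is in the Sample size calculation section: "Assuming that the proportion of all-cause mortality is 12% in severe or critically ill patients infected with COVID-19 under standard therapy". The trial has a single arm.

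**The concern.** Membership of the PPS depends on something that happens after baseline, and here that something can be the endpoint itself. A patient who dies on day 4 of a 7-day course leaves both numerator and denominator. Course length adds a second dependence. A death on day 10 stays in the set if the course ended at day 7, and leaves it if the investigator had extended treatment to day 14, in an open-label trial.

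The 12% reference carries no condition of surviving a treatment course, and no control arm exists in which the same removal would act. A PPS mortality below 12% could therefore arise with no drug effect, and a reader could take it as supporting the FAS result. The same rule touches 60-day mortality and clinical deterioration.

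**Working it through.** **Inputs from the article.** Reference mortality 12%, expected mortality on drug 2%, type I error 0.05, power 80%, 58 evaluable and 64 recruited, exact method (Sample size calculation). Course of 7 days, up to 14 (Intervention).

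**Input not in the article.** f, the share of 30-day deaths that fall within the patient's own course. It is assumed and varied. With deaths spread evenly over 30 days, f = 7/30 = 23% if all courses last 7 days, and f = 14/30 = 47% if all last 14. A value of 10% is shown for later-occurring deaths.

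**Step 1: the plan's own figure.** For an exact binomial test of 12% against 2% with lower tail 0.025 (two-sided 0.05), the smallest n with at least 80% power is 58. It passes with 2 or fewer deaths: P(X ≤ 2 | 58, 0.12) = 0.0239 and P(X ≤ 2 | 58, 0.02) = 0.890. The stated 58 is reproduced. A one-sided 0.05 test would need only 38, so the 0.025 tail is used below.

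**Step 2: expected PPS mortality, inactive drug, protocol-directed stops counted as completion.** The share of patients removed is 0.12f, all of them deaths, so

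PPS mortality = 0.12(1 − f) / (1 − 0.12f).

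- f = 10%: 0.108 / 0.988 = 10.9%
- f = 23% (7/30): 0.092 / 0.972 = 9.5%
- f = 47% (14/30): 0.064 / 0.944 = 6.8%

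With 64 dosed, 64 × 0.12 = 7.7 deaths are expected. The PPS loses 0.8, 1.8 and 3.6 of them respectively.

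**Step 3: chance of falling significantly below 12%.** Let D1 ~ Bin(64, 0.12f) be deaths on treatment and m = 64 − D1 the PPS size. Later deaths are D2 ~ Bin(m, PPS mortality). The PPS passes if P(X ≤ D2 | m, 0.12) ≤ 0.025. Summing over D1:

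| Set | Expected mortality | Chance of passing |
|---|---|---|
| FAS | 12.0% | 1.3% |
| PPS, f = 10% | 10.9% | 2.6% |
| PPS, f = 23% | 9.5% | 5.8% |
| PPS, f = 47% | 6.8% | 20.4% |

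**Step 4: if early stops also count as non-completion.** Let s be the share of all patients removed in this way who are alive at day 30. Then

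PPS mortality = 0.12(1 − f) / (1 − 0.12f − s),

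which exceeds 12% once s > 0.88f. The threshold is 8.8% of patients at f = 10%, 20.5% at f = 23% and 41% at f = 47%. At f = 23%:

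- s = 10%: 0.092 / 0.872 = 10.6%, chance of passing 2.5%
- s = 20%: 0.092 / 0.772 = 11.9%, chance of passing 1.4%

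**Step 5: one data set.** Suppose 5 of 64 die (7.8%, lower-tail p = 0.20). With one death on treatment the PPS shows 4/63 = 6.3% (p = 0.11). With two it shows 3/62 = 4.8% (p = 0.051). The percentage moves visibly, but neither case crosses 0.025.

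**The case against.** **The direction is not fixed by the wording.** A literal reading that removes deaths could equally remove patients stopped for viral clearance or for an adverse event, and swabs on days 3, 5 and 8 make clearance stops during the course likely. A reader might infer that PPS mortality must always fall below the reference. Step 4 shows that it need not. This stands. The downward bias holds on the ordinary reading, in which stopping as the protocol directs is completing, and the article does not say which reading applies.

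**The sentence is a summary.** Detailed rules for the PPS are commonly left to the analysis plan, and the sentence does not say outright that deaths are excluded. That is fair as to detail. But the rule printed here is completion, with no exception for death, and an analysis plan that follows it inherits the problem.

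**The sound result is already planned.** The FAS keeps every on-treatment death. A reader might infer that the primary result is biased, or that the article gives both sets equal weight. It supports neither: the FAS estimate is untouched, and no ranking is stated in either direction. What remains is that nothing marks the PPS figure as supportive.

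**No decision hangs on it.** The trial is exploratory, and the Statistical analysis section names no test of 30-day mortality against 12%. The pass rates in Step 3 rest on a test inferred from the sample size section. The shift in the percentage needs no test.

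**The largest figures are extreme.** The 47% share requires every patient to be extended to 14 days, whereas the default is 7. At f = 10% the pass rate of 2.6% is essentially nominal. Both points stand.

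**Conclusion.** The point holds, confined to the PPS results for 30-day mortality, 60-day mortality and clinical deterioration. On the plain reading the endpoint event can itself decide membership of the set, and the article makes no exception for death.

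If protocol-directed stops count as completion, an inactive drug with 12% mortality shows 10.9% at f = 10% and 9.5% at f = 23%. Under an even spread of deaths the outer limit is 6.8%, with all patients extended. The corresponding chances of falling significantly below 12% are 2.6%, 5.8% and 20.4%, against 1.3% in the FAS. If those stops also exclude survivors, the bias shrinks, and it reverses once they exceed about 0.88f of all patients.

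The size rests on f, which the article does not give, and on 64 patients being dosed. Deaths after a patient's own course ends stay in the PPS.

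**What to change.** For 30-day mortality, 60-day mortality and clinical deterioration, redefine the set along these lines: *PPS: FAS patients without serious protocol violation who took the doses scheduled while alive, or until a stop directed by the protocol (viral clearance or grade 3–4 drug-related adverse event). Death during treatment counts as an event and is not a reason for exclusion.* State that the FAS is primary and the PPS supportive.

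If a completers-only set is kept, label its result as mortality among patients alive at the end of treatment and do not set it against 12%.

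The cost is one definition and one sentence, with no new data. The Trial status section reports recruitment as complete ("with 64 participants recruited by 16 May 2023"), so 60-day follow-up ends around mid-July 2023, and the change should be made before analysis. The downside is that, where deaths on treatment are the main reason for removal, the PPS figure becomes less favourable and closer to the FAS.
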